## Abstract

**Background::**

Stanford type-A acute aortic dissection (AAD) is a severe cardiovascular disease demonstrating the characteristics of acute onset and rapid development, with high morbidity and mortality. The available evidence shows that preoperative acute lung injury (ALI) induced by Stanford type-A AAD is a frequent and important cause for a number of untoward consequences. However, there is no study assessing the incidence of preoperative ALI and its independent determinants before Standford type-A AAD surgery in Chinese adult patients.

**Methods/design::**

This is a prospective, double-blind, signal-center clinical trial. We will recruit 130 adult patients undergoing Stanford type-A AAD surgery. The incidence of preoperative ALI will be evaluated. Perioperative clinical baselines and serum variables including coagulation, fibrinolysis, inflammatory, reactive oxygen species, and endothelial cell function will be assayed. The independent factors affecting the occurrence of preoperative ALI will be identified by multiple logistic regression analysis.

**Trial registration::**

ClinicalTrials.gov (https://register.clinicaltrials.gov/), Registration number NCT01894334.

## Background

1

Patients presenting with aortic dissection within 2 weeks of the onset of symptoms are considered to have acute aortic dissection (AAD).^[1]^ AAD is a severe cardiovascular disease demonstrating the characteristics of acute onset and rapid development, with high morbidity and mortality. It has been shown that mortality of patients with AAD per hour early after the onset of symptoms is about 1% to 2%. Furthermore, mortality of patients with AAD who do not receive surgery is 58.0% in contrast to 26% in surgically treated patients.^[2,3]^ In patients with AAD, multiple organ failure including acute lung injury (ALI) is frequent.^[4,5]^ It is reported that 51% of patients meet the criterion of oxygenation impairment (oxygen fraction [PaO_2_/FiO_2_] ≤ 200 mm Hg) within 24 hour after onset of distal type AAD.^[6]^ Actually, preoperative ALI has been shown as a frequent complication associated with a number of untoward consequences, such as prolonged ventilator support, longer stay in intensive care unit and hospital, and even induces death. The previous work by Wang et al^[7]^ showed that the incidence of postoperative hypoxemia was up to 49.5% in Chinese adult patients undergoing Stanford type-A AAD surgery and postoperative hypoxemia was attributable to preoperative disturbance in oxygenation (78.5%, PaO_2_/FiO_2_ ≤ 200 mm Hg). In addition, preoperative hypoxemia can also result in surgery delay, which increases the risk of aortic rupture, cardiac tamponade, or even death. Therefore, the prophylaxis and/or treatment of preoperative ALI induced by AAD is important for final outcomes of patients.

Better understanding of the pathophysiology of preoperative ALI in the patients with AAD can improve clinical prophylaxis and/or treatment, but its underlying molecular and cellular mechanisms remain largely unknown. It is reported that the occurrence of oxygenation impairment on hospital days 2.5 in patients with Standford type-B AAD can be predicted by a multivariate logistic regression model.^[8]^ To our best knowledge, however, there is no study having assessed whether the preoperative ALI in Chinese adult patients undergoing the Standford type-A AAD surgery can be predicted by preoperative clinical and basic assessments. Thus, we put forward a prospective study strategy aiming to address the above issues.

## Aims

2

The aims of this study are to clarify the incidence, independent risk factors, and possible mechanisms of preoperative ALI in Chinese adult patients undergoing the Standford type-A AAD surgery. This will include a detailed statistical analysis of perioperative clinical baselines and serum variables, such as coagulation, fibrinolysis, inflammatory, reactive oxygen species, and endothelial cell function. The outcomes of this study will obtain the details regarding the incidence, independent predictors, and pathophysiological mechanisms of preoperative ALI, which will benefit the prophylaxis and/or treatment of preoperative ALI induced by Standford type-A AAD.

## Methods

3

### Design of trial

3.1

This trial is a prospective, double-blind, signal-center clinical trial which had been registered at www.clinicaltrials.gov (identifier NCT01894334) and approved by the Beijing Anzhen Hospital Clinical Research Ethics Committee (Fig. 1).

**Figure 1 F1:**
[figure not shown]
The flowchart of the trial.

### Participants (inclusion and exclusion criteria)

3.2

The sample of subjects is estimated to 130 patients, based on a 79% incidence of ALI before surgery in patients with Stanford type-A AAD^[7]^ and the set power to 80% for a type I error of 5% (Power Analysis and Sample Size, PASS V11.0, NCSS, LLC. Kaysville, UT). A convenient sample will be recruited from the Beijing Anzhen Hospital. The AAD surgery in the Beijing Anzhen Hospital is performed in approximately 300 cases per year. If 30% of these patients are eligible and consent, we will meet our recruitment target in about 1.5 years, which can avoid the bias from the different levels of surgical procedures in different periods.

Patients aged 18 to 75 years will be included. The patients with coronary heart disease; heart failure; severe cardiac tamponade; unstable hemodynamics; nervous system abnormalities; clinically apparent malperfusion^[9]^ including lower limb, cerebral, coronary, and renal malperfusion; and visceral ischemia will be excluded. All patients enrolled in this study have normal hepatic and renal function according to the preoperative physical and laboratory examinations. No patient is prescribed with nonsteroidal anti-inflammatory drugs or corticosteroids before or after admission. All patients will be informed and consented with regard to their participation in the study.

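### A convenience sample does not protect the ALI incidence from selection among the hospital's own eligible patients; the size of any bias is unknown, and consecutive enrolment would remove most of the doubt

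*Protocol article*

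**What the plan says.** Section 2 (Aims) names the incidence first: "The aims of this study are to clarify the incidence, independent risk factors, and possible mechanisms of preoperative ALI". The abstract also lists evaluation of the incidence among the methods.

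Section 3.2 (Participants) gives the sampling rule: "A convenient sample will be recruited from the Beijing Anzhen Hospital". The same paragraph sets the size ("The sample of subjects is estimated to 130 patients", "based on a 79% incidence of ALI before surgery in patients with Stanford type-A AAD") and the recruitment outlook: "The AAD surgery in the Beijing Anzhen Hospital is performed in approximately 300 cases per year", and "If 30% of these patients are eligible and consent, we will meet our recruitment target in about 1.5 years".

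The article nowhere mentions consecutive enrolment.

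**The concern.** An incidence can be interpreted only if, among eligible patients, being enrolled does not depend on having the condition. A convenience sample gives no such assurance, because the rule leaves open which eligible patients are approached. If enrolment is related to ALI in either direction, the observed proportion moves away from the true one. The confidence interval does not show this, and more patients would only narrow the interval around the shifted value.

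This is separate from the claim of national representativeness in section 6. Dropping that claim would limit the result to this hospital, but selection among the hospital's own eligible patients would remain.

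At stake is the incidence estimate. Selection on ALI status alone would change the intercept of the logistic model in section 5, not its odds ratios, so the point does not extend to the predictor analysis on this ground.

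**Working it through.** **Inputs from section 3.2:** 300 operations per year; 30% eligible and consenting; target 130; assumed ALI incidence 79%; about 1.5 years. **Assumption, not in the document:** r, the enrolment rate of ALI patients divided by that of non-ALI patients.

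**1. The plan's own timeline.** 300 × 0.30 = 90 patients per year, and 130 / 90 = 1.44 years, which agrees with about 1.5. In 1.5 years 90 × 1.5 = 135 patients are expected, and 130 / 135 = 96.3%. The 30% has two readings:
- It counts every eligible and willing patient. The projection then presumes near-consecutive enrolment.
- It is the enrolment yield, with patients never approached already removed. The projection then fits any sampling method.

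**2. Sampling error.** The 95% half-width is 1.96 × √(0.79 × 0.21 / 130) = 0.070, so the interval is 72.0% to 86.0%.

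**3. Shift from selection.** With true incidence 79%, the apparent incidence is 0.79r / (0.79r + 0.21).

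| r | Apparent incidence | Shift (points) |
|---|---|---|
| 0.5 | 65.3% | −13.7 |
| 0.8 | 75.1% | −3.9 |
| 1.25 | 82.5% | +3.5 |
| 2.0 | 88.3% | +9.3 |

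To reach the interval limits, r = (0.72 / 0.28) × (0.21 / 0.79) = 0.68 or r = (0.86 / 0.14) × (0.21 / 0.79) = 1.63. A shift of more than 7 points therefore needs r below about 0.68 or above about 1.63.

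**4. How many eligible patients must be missed for that.** For r below 1, the largest possible enrolled share has all non-ALI patients enrolled: 0.21 + 0.79r. For r above 1, it has all ALI patients enrolled: 0.79 + 0.21 / r.
- r = 0.68 (unrounded 0.6835): at most 0.21 + 0.79 × 0.6835 = 75.0%, so at least a quarter are missed.
- r = 1.63 (unrounded 1.633): at most 0.79 + 0.21 / 1.633 = 91.9%, so at least 8% are missed. At that limit every missed patient is free of ALI.
- r = 0.5: at most 60.5%. r = 2.0: at most 89.5%.

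The same condition can be put as a difference in ALI rate between enrolled and missed patients, since bias = (1 − share enrolled) × difference. A 7-point shift needs a difference of 70 points at 90% enrolled, 35 at 80%, 23 at 70% and 14 at 50%.

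**5. Under near-consecutive enrolment.** If 79% of 135 patients have ALI, that is 106.65. Enrolling 130 and missing 5 gives at least (106.65 − 5) / 130 = 78.2% and at most 106.65 / 130 = 82.0%. The shift is at most about 3 points, inside the half-width. This bounds selection after consent only; selection at the consent step lies inside the 30%.

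**The case against.** Three stronger readings are tempting, and the document supports none of them.

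**That the recruitment arithmetic contradicts the sampling rule.** A reader might infer that needing 96.3% of the eligible and consenting patients excludes a convenience sample. But a patient who is never approached cannot consent, so the 30% can be read as the yield after non-approach. On that reading 135 against 130 shows only that the timeline is feasible. The sentence is also conditional. The projection presumes near-consecutive enrolment only if the 30% means all eligible and willing patients.

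**That the incidence will be wrong by 9 to 14 points.** Those shifts come from r = 2.0 and r = 0.5, values with no anchor in the document, and they need enrolled shares of at most 89.5% and 60.5%. They cannot occur together with 96.3% capture, where the limit is about 3 points. The two belong to different scenarios.

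**That the article itself shows selective approach.** Section 1 says that "preoperative hypoxemia can also result in surgery delay", but not that delayed patients go unapproached; delay could as well leave more time for consent. Section 4 provides a legally responsible substitute for a participant who cannot attend an assessment, which helps to keep such patients in. The sampling sentence may also mean only that the hospital is a convenient source.

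It is also fair to say that a screening log and out-of-hours procedures belong to a full protocol, so their absence from an article is no fault. All of this limits the size and certainty of the point. What stands is that the sampling rule is stated, is not omitted detail, and is a poor one for estimating an incidence.

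**Conclusion.** The point holds as a weakness of the stated design, not as a demonstrated contradiction or a demonstrated bias. The convenience rule leaves the incidence open to ALI-related selection that an interval of about ±7.0 points does not cover. The size is unknown, because the document gives neither the share of eligible patients enrolled nor the ALI rate in those missed.

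Taking 79% as the true incidence and r as an assumption, moderate selection (0.8 to 1.25) costs about 4 points, which is inside the interval. A shift beyond 7 points requires that at least about a quarter of eligible patients are missed if ALI patients are under-enrolled, or at least about 8% if they are over-enrolled. If enrolment is in practice near-consecutive, the sampling sentence merely describes it badly and needs only correction.

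**What to change.** In section 3.2, replace the sampling sentence with: *Consecutive eligible patients with Stanford type-A AAD will be approached until 130 are enrolled.* Report the numbers eligible, approached and enrolled alongside the incidence, so that a reader can judge how much selection is possible, including at the consent step.

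This costs one sentence and a simple count, with no additional patients. The small downside is seeking consent and processing samples out of hours. If consecutive approach is not feasible, describe the result as the proportion with ALI among enrolled patients, not as an incidence.

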### Surgical procedure^[10,11]^

3.4

Patients undergo median sternotomy and CPB. Cannulation of the femoral artery and/or right axillary artery will be performed for CPB. Furthermore, the right axillary artery cannulation will also be carried out for selective cerebral perfusion. After CPB is established and cooling is initiated, the ascending aorta will be clamped and cardiac arrest will be accomplished with cold cardioplegic solution during the cooling phase. When the nasopharyngeal temperature is decreased to 20 °C to 25 °C, circulatory arrest will be instituted. A stent graft and a 4-branch prosthetic graft will be used for arch replacement. After the open distal anastomosis is completed, the 4-branch prosthetic graft will be cross-clamped. Then the blood perfusion of the lower body will be started via the perfusion limb of the 4-branch prosthetic graft. Selective cerebral perfusion will be continued until the anastomosis to the left common carotid artery, innominate artery, and left subclavian artery is accomplished. Then CPB will be resumed to normal flow, and rewarming will be started. Valve-sparing root resection (aortic valve plasty, the David procedure, or valsalva sinus plasty) or valve graft replacement will be performed according to the subtype of the aortic root.

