### Definitions

3.5

In all patients, the diagnosis of AAD will be confirmed by history, chest radiography, transthoracic, and contrast-enhanced computed tomogrphy or magnetic resonance imaging. The dissection is considered as AAD if the time from the onset of the symptoms to surgery is 14 days or less. This study will only include the type-A AAD according to the Stanford classifications.^[1,2]^

The definition criteria of the ALI includes an acute hypoxemic respiratory insufficiency with bilateral pulmonary infiltrates, but is not caused by left atrial hypertension according to the left ventricular ejection fraction (LVEF). The ALI will be defined using Murray lung injury score (Murray LIS).^[12,13]^ Murray LIS consists of 4 distinct clinical parameters, including the bilateral infiltrates observed on chest radiograph, oxygenation index (PaO_2_/FiO_2_ ratio), lung compliance, and PEEP value. The severity of ALI was quantified as follows: no = the Murray LIS 0, mild to moderate = the Murray LIS 0.1 to 2.5, and acute respiratory distress syndrome = the Murray LIS > 2.5. The Murray LIS will be calculated using a specially designed tool on the web site (http://med.39.net/tools/murray.html).

Hypertension is defined as systolic blood pressure ≥140 mm Hg and/or diastolic blood pressure ≥90 mm Hg, or the need of antihypertensive agents.^[14]^ Diabetes mellitus is defined as fasting glucose level ≥126 mg/dL (7.0 mmol/L), or a glycosylated hemoglobin (Hb) ≥6.5%,^[15]^ or treatment with oral hypoglycemic agents or insulin. Smoking status will be defined as current smokers according to self-report. A glomerular filtration rate less than 60 mL/min/1.73 m^2^, and increase in serum creatinine by more than 50% times baseline is defined as impaired renal function.^[16]^

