## Statistical analysis

5

The data obtained in this study will be analyzed using SPSS 18.0 (SPSS Inc., Chicago, IL). Univariate and multiple logistic regression analyses will be used to determine the independent predictors of preoperative ALI. Univariate analysis will be applied for demographic data (age, sex, and BMI), comorbidities (smoking history, hypertension, and diabetes), preoperative data (hemodynamics, onset of symptoms to surgery, aortic diameter, LVEF, LVEDd, and EuroSCORE), surgical data (surgery time, hypothermic circulatory arrest time, intravenous colloid, crystalloid, and transfusion volumes), postoperative variables (intravenous colloid, crystalloid and transfusion volumes, urine volume, seroma volume of drainage, mechanical ventilation time, and in-hospital mortality), and serum measurements before surgery (coagulation/fibrinolysis, inflammatory, ROS, platelet, and endothelial cell function). In univariate analysis, variables associated with preoperative ALI with a *P* value <0.10 will be selected. Then, these selected variables will be put into the multiple logistic regression analysis to identify the independent predictors of preoperative ALI.

Receiver operating characteristic curve will be used to test discrimination of multivariate regression model and to determine the cutoff value in predicting preoperative ALI with sensitivity and specificity, respectively. The missing values will be displaced by means according to Intention-To-Treat rules. A *P* value <0.05 will be considered statistically significant.

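### Pre-existing lung disease and lung infection are neither excluded, recorded nor modelled, so the lung score cannot separate them from dissection-induced ALI

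*Protocol article*

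**What the plan says.** All references are to the protocol article.

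- **Eligibility (section 3.2).** The exclusions open with "The patients with coronary heart disease; heart failure; severe cardiac tamponade; unstable hemodynamics; nervous system abnormalities; clinically apparent malperfusion" and end with visceral ischemia. The section adds that "All patients enrolled in this study have normal hepatic and renal function according to the preoperative physical and laboratory examinations", and that no patient is on nonsteroidal anti-inflammatory drugs or corticosteroids. No lung condition appears.
- **Outcome (section 3.5).** ALI is first described as "an acute hypoxemic respiratory insufficiency with bilateral pulmonary infiltrates", with one alternative cause set aside: "but is not caused by left atrial hypertension according to the left ventricular ejection fraction (LVEF". The same paragraph then says "The ALI will be defined using Murray lung injury score". Only a score of 0 is graded as no injury; 0.1 to 2.5 is mild to moderate.
- **Measurement (section 4.2.5).** The score combines the admission radiograph, the oxygenation ratio, compliance and PEEP.
- **Second review (section 4).** An independent expert, blinded to the first adjudication, reviews all ALI cases and a random sample of non-cases. No criterion on cause is stated.
- **History and covariates (sections 4.1 and 5).** Section 4.1 lists body size, regular drugs, smoking, hypertension and diabetes. Section 5 lists "comorbidities (smoking history, hypertension, and diabetes" as the comorbidities.
- **Purpose (section 2).** The results "will benefit the prophylaxis and/or treatment of preoperative ALI induced by Standford type-A AAD".

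**The concern.** The eligibility rules screen the heart, nervous system, liver, kidneys and anti-inflammatory drug use, but not the organ that is scored. The outcome is a composite of lung measurements that other lung conditions can also disturb, and the threshold for a case is any value above 0. A patient who arrives with pneumonia, aspiration or chronic lung disease can therefore become a case without any contribution from the dissection. Because the listed history does not capture these conditions, such patients could not be identified, adjusted for or set aside at analysis.

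The aims attribute the injury to the dissection and look for its mechanisms. The blood panel in section 4.5 includes interleukin-6, tumor necrosis factor α, myeloperoxidase and white cells. Lung infection can raise these and worsen the lung score together, so an infection signal could be read as a dissection mechanism. Smoking could likewise appear as a predictor through lung disease that nobody recorded.

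**Working it through.** **Text check.** I looked for a step at which another lung cause would be caught.

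| Step | Handles another lung cause? |
|---|---|
| Exclusions (3.2) | No lung item. The corticosteroid rule removes some treated chronic disease only. |
| ALI description (3.5) | The requirements that it be acute and bilateral would remove some cases if applied. The only cause ruled out is left atrial hypertension. |
| Score grading (3.5, 4.2.5) | No. Any score above 0 counts, and no component identifies cause or onset. |
| Second review (4) | Possibly, but no rule on cause is stated. |
| History (4.1) | Smoking and regular drugs only; no lung disease or infection. |
| Candidate predictors (5) | Smoking and white cells at most, as rough proxies. |

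The plan gives no figure on this point to reproduce. The sizes below are illustrations.

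**Incidence.** From section 3.2: p = 0.79 and N = 130. Assumed: a share q of patients has another lung condition that alone gives a positive score, independently of dissection-induced injury. The documents give no value for q.

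Observed incidence = p + (1 − p)q. Patients whose status changes = N(1 − p)q. Share of cases carrying the other condition = q / observed incidence.

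| q | Observed incidence | Patients changed | Patients with the condition | Share of cases |
|---|---|---|---|---|
| 5% | 0.79 + 0.21 × 0.05 = 80.1% | 1.4 | 6.5 | 6.2% |
| 10% | 0.79 + 0.21 × 0.10 = 81.1% | 2.7 | 13 | 12.3% |
| 20% | 0.79 + 0.21 × 0.20 = 83.2% | 5.5 | 26 | 24.0% |

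For comparison, the 95% half-width for 79% at N = 130 is 1.96 × √(0.79 × 0.21 / 130) = 7.0 points. A shift of 2.1 points at q = 10% lies well inside it.

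**Markers.** Under the same assumption every patient with the other condition is a case, so at q = 10% it is present in 12.3% of cases and in no non-case. If the condition raises the mean of a marker by δ, cases exceed non-cases by 0.123δ on average, even if the marker has nothing to do with the dissection. The documents give no δ, so I cannot say whether this would pass the P < 0.10 screen.

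**Smoking.** Assume the other condition affects 20% of smokers and 5% of non-smokers, smoking has no effect on dissection-induced ALI (true OR 1.0), and there are 65 patients in each group.

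- With p = 0.79: smokers 0.79 + 0.21 × 0.20 = 0.832; non-smokers 0.79 + 0.21 × 0.05 = 0.8005. OR = (0.832/0.168)/(0.8005/0.1995) = 1.23. SE of log OR = √[1/(65 × 0.832 × 0.168) + 1/(65 × 0.8005 × 0.1995)] = 0.45, so z = 0.210/0.454 = 0.46.
- With p = 0.70: 0.760 and 0.715, OR = (0.760/0.240)/(0.715/0.285) = 1.26, SE 0.40, z = 0.58.

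The chance of passing a two-sided P < 0.10 screen is P(Z > 1.645 − z) + P(Z < −1.645 − z). It rises from 10% to about 14% and 16% respectively. The bias is real but modest at this sample size.

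**The case against.** The strongest reply is that section 3.5 must be read whole. Nothing says that the score replaces the requirement for an acute, bilateral process. If that requirement is applied, long-standing emphysema, an earlier resection, a unilateral effusion and a lobar pneumonia would not qualify, and mainly bilateral pneumonia or aspiration would remain. The second reviewer, who sees every ALI case, is also a natural person to reject other causes. This narrows the point but does not close it: the grading by score does not enforce either word, the reviewer is given no criterion on cause, and the listed history would not supply the information needed to apply one.

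A second reply is that this is a condensed article. The full protocol and the flowchart are not shown and may contain more. That is fair as a caution. But the article does print an exclusion list, a history list and a comorbidity list, and lung disease is absent from all three.

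Three stronger readings are tempting and are not supported:

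- **That these patients must be excluded.** The aim includes incidence in adults coming to type-A surgery. Including all comers is defensible, and exclusion would narrow that population.
- **That the incidence will be seriously inflated, or smoking will be a false predictor.** Every prevalence used is assumed, and under those assumptions both effects are small.
- **That acute aortic regurgitation is another unscreened cause.** Section 3.4 foresees valve work ("Valve-sparing root resection (aortic valve plasty, the David procedure, or valsalva sinus plasty) or valve graft replacement will be performed"), but regurgitation in type-A dissection is usually a consequence of the dissection, so it is not a competing lung disease. Whether LVEF can rule out left atrial hypertension is a separate question.

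**Conclusion.** The point holds in limited form. As printed, the plan neither excludes nor records nor models pre-existing lung disease or lung infection, and it turns ALI into a score that does not identify cause. Some patients can therefore be counted as having dissection-induced injury when another lung condition explains the score. How many depends on how strictly the general description and the second review are applied, which the article does not fix.

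The likely effect on incidence is small: 79% becomes 80.1% to 83.2% for an assumed 5% to 20% of patients affected, each assumed to score positive from that condition alone and independently of the dissection. The more important risk is to interpretation of the predictors, above all the inflammatory markers, and its size cannot be derived from the documents. This is a worthwhile, cheap improvement and not a flaw that invalidates the design.

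**What to change.** 1. **Section 4.1:** record known chronic lung disease, prior lung resection, and pneumonia or aspiration diagnosed at or before admission. Take these from the history and from the diagnostic CT or chest film already obtained.
2. **Section 5:** add this information as a candidate covariate, and report incidence and the predictor model with and without these patients. If nearly all of them score above 0, the covariate will almost perfectly predict the outcome and its coefficient will be unstable; the with-and-without comparison then carries the message.
3. **Section 4:** give the second reviewer the same written criterion on cause.

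The cost is a few extra fields and one sensitivity analysis on fewer patients. If 10% were set aside, 117 would remain and the half-width for 79% would widen from 7.0 to 1.96 × √(0.79 × 0.21 / 117) = 7.4 points. Recording loses no recruits. If the sponsor chose exclusion instead, recruitment at 300 × 0.30 = 90 a year would go from 130/90 = 1.44 years to 130/81 = 1.60 years at a 10% loss.
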